#### Secondary Outcome Measures

The secondary outcomes are as follows:

1. The NRS score at rest and during movement at 2 hours after surgery.

2. The NRS score at rest and during movement at 48 hours after surgery.

3. The cumulative consumption of opioids, such as pethidine, sufentanil, and morphine, during the first 48 hours after the operation.

4. The number of patients who required additional analgesics, such as opioids (pethidine, sufentanil, or morphine) or nonsteroid anti-inflammatory drugs (acetaminophen or diclofenac) during the first 48 hours after the operation.

5. The total consumption of opioids (pethidine, sufentanil, and morphine) or nonsteroid anti-inflammatory drugs (acetaminophen and diclofenac) during the first 48 hours after the operation.

6. The incidence of nausea and vomiting and adverse central nervous system events at 2, 24, and 48 hours after the operation.

The use of rescue analgesic drugs (types, administration times, and doses) and any adverse side effects (yes or no) will be recorded.

### Participant Timeline

The participant timeline is shown in Table 1.

**Table 1 table1:** Schedule of enrollment, interventions, and assessments for the trial.

			Study period													
			Enrollment		Allocation		Postallocation									Close-out
Time points^a^			–*t_1_*		0		*t_1_*		*t_2_*		*t_3_*		*t_4_*		*t_5_*	
**Enrollment**																
	Eligibility screen	X														
	Informed consent	X														
	Allocation			X												
**Interventions**																
	S(+)-ketamine					X		X		X		X				
	Normal saline					X		X		X		X				
**Assessments**																
	NRS^b^ pain score									X		X		X		
	Postoperative opioid^c^ consumption									X		X		X		
	Patients who required additional analgesics									X		X		X		
	Postoperative nausea									X		X		X		
	Postoperative vomiting									X		X		X		
	Nightmares									X		X		X		
	Hallucinations									X		X		X		
	Dizziness									X		X		X		
	Itchy skin									X		X		X		

^a^The following time points were used: *–t_1_*, preoperative assessment; 0, entering the operating room; *t_1_*, after induction; *t_2_*, end of surgery; *t_3_*, 2 hours after surgery; *t_4_*, 24 hours after surgery; and *T_5_*, 48 hours after surgery.

^b^NRS: numeric rating scale.

^c^Opioids included pethidine, sufentanil, or morphine.

### Safety

The main adverse effects of S(+)-ketamine alone are neuropsychiatric symptoms, such as dizziness. Therefore, S(+)-ketamine is usually used with midazolam and propofol to decrease its psychoactive effects. All adverse events related to this research will be investigated and recorded by research personnel from the time patients sign the informed consent to the end of follow-up. The investigator will decide whether to continue the study according to the status of the patient. Any serious adverse events will be treated with appropriate interventions and submitted to the principal researcher and the Medical Ethics Committee within 24 hours.

### Ethical Considerations

This study has been approved by the Medical Ethics Committee of the First Affiliated Hospital of Shandong First Medical University under approval number YXLL-KY-2021 (077) and will be performed in accordance with the approved guidelines and regulations of the participating institutions. The study was registered at ClinicalTrials.gov (NCT05289050) on February 26, 2022. Informed written consent will be obtained from all patients before inclusion in the study. Because the involvement of the patients is voluntary, the study can be stopped at any time.

### Data Management

The basic information of the patients before surgery and the dosage of drugs used during the operation will be collected by the anesthesiologists participating in surgical anesthesia, and the follow-up data after surgery will be provided by independent researchers. Each data point related to the study will be entered into the case report form to improve data completeness and accuracy, and electronic data will be collected and analyzed by statisticians. All the clinical trial materials will be stored securely.

### Statistics

The SD will be described for measurement data that follow a normal distribution, and the median (IQR) will be described for measurement data that do not conform to a normal distribution. The student *t* test will be used to compare continuous and normally distributed variables, and the Mann-Whitney U test will be used to compare nonnormally distributed variables. Counts (percentages) will be described for categorical variables using χ^2^ analysis or Fisher exact tests for compilation.

Both primary and secondary outcomes will be based on an intention to treat analysis. SPSS 22.0 software (IBM) will be used for statistical analysis, and a *P* value of <.05 will be considered to be statistically significant.

### Sample Size

The minimum clinically important difference (MCID) can be used to guide the noninferiority margin for clinical trials and to determine the sample size in a clinical trial [16,17]. The NRS pain score ranges from 0 (no pain) to 10 (worst pain imaginable). The MCID for the NRS that was used for the calculation of the study sample size was 1.3; however, some studies suggest that an MCID of 1.5 or 2 is appropriate [18-20]. The sample size would have been too small if we choose an MCID of 2. Considering a 10% withdrawal or dropout rate, a sample size of 72 patients per group was calculated, with a power of 80%. The MCID determined 1.5 as statistically significant, with an SD of 3 at the 5% bilateral significance level.

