## Methods

### Objective and Trial Design

This clinical study was designed to observe the analgesic effect of a lower intravenous dose of S(+)-ketamine (0.3 mg/kg/h) in patients after TKA surgery.

This is a single-center, randomized, single-blind, controlled, clinical trial in older patients undergoing TKA under general anesthesia. Eligible patients will be randomized to receive S(+)-ketamine (n=72) or a placebo equivalent, 0.9% sodium chloride (n=72), in a ratio of 1:1. Patients will be randomized using a computer-generated list. The anesthetist nurse and the pharmacist will not be blinded and will not partake in the following research, but the follow-up evaluators will be blinded in the trial.

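### The sample-size paragraph names two design differences, 1.3 and 1.5 NRS points; the stated 72 per group and 80% power follow from 1.5 and do not hold for 1.3

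*Protocol article*

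**What the plan says.** All the relevant text is in the Sample Size section of the protocol article, apart from the group sizes, which are repeated under Objective and Trial Design.

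- On the basis of the calculation: "The MCID for the NRS that was used for the calculation of the study sample size was 1.3". The same sentence goes on to say that other studies favour 1.5 or 2. The next sentence rejects 2 because the sample would be too small.
- On the result: "Considering a 10% withdrawal or dropout rate, a sample size of 72 patients per group was calculated, with a power of 80" (per cent).
- On the remaining inputs: "The MCID determined 1.5 as statistically significant, with an SD of 3 at the 5% bilateral significance level".
- On allocation: "Eligible patients will be randomized to receive S(+)-ketamine (n=72) or a placebo equivalent, 0.9% sodium chloride (n=72), in a ratio of 1:1".

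The section explains why 2 was not chosen. It does not say that 1.3 was set aside, and it gives no reason for moving from 1.3 to 1.5.

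**The concern.** A sample-size calculation for two means rests on one target difference. Here one sentence says that 1.3 was the value used, and another lists 1.5 beside the SD and the significance level. Both cannot be the input that produced 72 per group.

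The target difference defines what the 80% power refers to. A reader who takes the 1.3 sentence at face value will believe that the trial has a 20% chance of missing a true difference of 1.3 points, when on the stated inputs that chance is nearer 30%. This affects how a non-significant primary result would be read.

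The closing sentence adds to the confusion. It speaks of the MCID as fixing what is statistically significant, whereas a design difference fixes power. Significance is defined separately in the Statistics section, as P<.05.

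**Working it through.** **Inputs (Sample Size section unless noted)**
- Difference Δ: 1.3 or 1.5 NRS points (both stated)
- SD: 3
- Significance level: 5%, two-sided
- Power: 80%
- Dropout: 10%
- Allocation: 1:1, 72 per group (Objective and Trial Design)
- Test: Student t test for normally distributed variables (Statistics)

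**Formulas**
- Normal approximation: n per group = 2 (1.960 + 0.842)² SD² / Δ²
- Exact version: the smallest n for which the two-sided t test with 2n − 2 degrees of freedom reaches 80% power, using the noncentral t distribution with noncentrality Δ / (SD √(2/n))
- Enrolled per group = n / (1 − 0.10), rounded up

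**Step 1. Reproduce the stated figure with 1.5**
- Normal: 2 × 7.85 × 9 / 2.25 = 62.8, so 63; 63/0.9 = 70.
- Exact t: 64; 64/0.9 = 71.1, so **72**. This is the stated figure.

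**Step 2. Repeat with 1.3**
- Normal: 2 × 7.85 × 9 / 1.69 = 83.6, so 84; 84/0.9 = 93.3, so 94.
- Exact t: 85; 85/0.9 = 94.4, so **95** per group, 190 in total against 144.

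**Step 3. Power of the stated design**

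The standard error of the difference is 3 √(2/64) = 0.530 with 64 per group and 3 √(2/72) = 0.500 with 72 per group.

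| True difference | Evaluable per group | Noncentrality | Power, exact t | Power, normal |
|---|---|---|---|---|
| 1.5 | 64 | 1.5/0.530 = 2.83 | 80.1% | 80.7% |
| 1.5 | 72 | 1.5/0.500 = 3.00 | 84.6% | 85.1% |
| 1.3 | 64 | 1.3/0.530 = 2.45 | 68.2% | 68.8% |
| 1.3 | 72 | 1.3/0.500 = 2.60 | 73.3% | 73.9% |

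**Step 4. Could 1.3 lead to 72 some other way?**
- A one-sided 5% test at 1.3 gives 66 by the normal approximation, or 74 after dropout. The text says "at the 5% bilateral significance level".
- An SD of 2.6 at 1.3 gives 63, or 70 after dropout. The text says SD 3.

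Each comes close to 72 only by departing from a stated input, so neither rescues the 1.3 sentence.

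**The case against.** The strongest reply is that nothing was miscalculated. The inputs in the closing sentence give exactly 72 per group, and the total of 144 agrees throughout the article. The paragraph can be read as a progression: it mentions 1.3, notes that others prefer 1.5 or 2, rejects 2 and settles on 1.5. On that reading the power of 68% describes a target that the trial never adopted. This largely stands. The likeliest explanation is that 1.5 was the design value and that the 1.3 sentence is a slip or a literature value. But the sentence says in terms that 1.3 was used for this calculation, so the contradiction remains on the page.

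Three stronger readings are tempting, and the article does not support them.

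- *Two MCIDs let the sponsor choose afterwards what counts as clinically important.* No section makes the MCID a criterion for success or interpretation. The MCID enters only in the sample-size calculation, and the stated criterion is P<.05.
- *The design is faulty because an observed difference well below 1.5 can be significant.* With 64 per group the threshold is 1.979 × 0.530 = 1.05 points. Any two-sided 5% design with 80% power behaves this way: the ratio is about 1.96/2.80 = 0.70, and 0.70 × 1.5 = 1.05. Only the wording that links 1.5 to significance needs correcting.
- *The mention of a noninferiority margin means that the wrong design was sized.* That sentence describes a general use of the MCID and does not call this trial a noninferiority trial.

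**Conclusion.** The point holds as an internal inconsistency in a stated design input. The Sample Size section offers 1.3 and 1.5 as the basis of one calculation, and only 1.5 gives 72 per group.

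A reader might infer that the claim of 80% power is simply false. It is not: it is correct for a true difference of 1.5 with 64 evaluable per group. It is wrong only if 1.3 is taken as the target, as one sentence invites. Power at 1.3 is then 68% with the planned dropout and 73% with none, and 80% would need 95 enrolled per group.

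These figures assume the stated SD of 3, a two-sided 5% level and the t test. The normal approximation changes them by less than one percentage point of power and by one or two patients per group, so the conclusion does not depend on the method.

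**What to change.** In the Sample Size section:

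1. Correct the sentence that names 1.3 as the value used, so that 1.5 is the single design difference (64 evaluable and 72 enrolled per group, SD 3, two-sided 5%, 80% power, 10% dropout).
2. Reword the closing sentence to say that 1.5 is the difference the trial is powered to detect, and leave the definition of significance to the Statistics section.
3. If 1.3 is to remain as the MCID, add that power at a true difference of 1.3 is about 68% with 10% dropout and 73% with none.

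This is a text correction. It adds no patients and leaves the test and the significance level unchanged. The only cost is a less favourable stated power if 1.3 is kept. The Results section reports 132 of the 144 patients enrolled by December 2023, so correcting the text is more practical than resizing the trial.

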## Results

The protocol was registered at ClinicalTrials.gov (NCT05289050) on February 26, 2022. It was performed in accordance with the approved guidelines and regulations of the participating institutions. Recruitment began in April 2022. Data collection is expected to conclude in September 2024. Study completion is expected in December 2024. As of December 2023, we have enrolled 132 patients.

## Discussion

TKA is increasingly performed in geriatric patients to cure pain, deformation, and the inability to walk normally caused by knee arthritis. The total number of TKA procedures may increase by 401% in 2040 compared to that in 2014 [21]. Poor management of acute pain after TKA increases the risk of complications, such as venous thrombosis, an inability to exercise effectively, and pneumonia. Currently, there is a consensus that inadequate postoperative pain control measures are being implemented, especially in older patients. Opioids are the main treatment for relieving TKA postoperative pain [22]. Considering the side effects of opioids, appropriate multimodal medication projects are required to decrease postoperative opioid use and improve effects with decreasing pain levels in geriatric patients. Ketamine can suppress the pathway of central sensitization and secondary postoperative hyperalgesia and has been proposed as a component of multimodal analgesia for various surgical procedures [23]. Ketamine in subanaesthetic doses is available as an adjuvant to the standard regimen of opioids, presenting prominent analgesic and opioid-sparing effects without adverse effects [24]. Some studies have shown that low-doses of S(+)-ketamine can reduce the incidence of side effects (eg, the induction of hypotension) and high doses of opioids through its sympathetic stimulation, analgesia, and antagonism of the NMDA receptor [25,26]. Similarly, a meta-analysis demonstrated that the administration of low-dose ketamine can decrease total opioid use and pain scores over 2 days and may also reduce postoperative nausea and vomiting. This has been attributed to reductions in total opioid administration, leading to decreased opioid-associated nausea and vomiting [27,28]. Another meta-analysis demonstrated that perioperative intravenous ketamine reduced postoperative opioid consumption by 8 mg morphine equivalents per day [29].

Additional studies have demonstrated that a low-dose intravenous infusion of ketamine can be administered as an adjuvant drug to alleviate acute postoperative pain, while the guidelines for ketamine for postoperative acute pain have found grade B evidence to advocate perioperative ketamine as an adjuvant [15,30].

Although low-dose S(+)-ketamine has been shown to be beneficial in pain management after various surgeries, there is no consensus regarding the effectiveness of an S(+)-ketamine analgesic combined with opioids in older patients with knee arthroplasty. In addition, the appropriate administration duration and dose of S(+)-ketamine to achieve pain relief in older patients are unknown. A randomized controlled trial will be conducted to assess the efficacy and safety of an intraoperative intravenous low-dose of S(+)-ketamine for pain management in older patients undergoing TKA.

The design of our protocol has several limitations. First, this is a single-center study with a relatively small sample size, and only older patients undergoing TKA will be enrolled, which limits the generalizability of our outcomes. Second, the end of our follow-up is 48 hours postoperatively. A longer follow-up is necessary to demonstrate the long-term effects and safety of S(+)-ketamine.

In conclusion, we will appraise the efficacy and safety of the intraoperative intravenous injection of S(+)-ketamine to relieve acute pain after TKA in older patients who may benefit from the administration of S(+)-ketamine.

## Abbreviations

HR: heart rate
MCID: minimum clinically important difference
NMDA: N-methyl-D-aspartate receptor
NRS: numeric rating scale score
TKA: total knee arthroplasty
